# A double-blind, randomised, placebo-controlled parallel study to investigate the effect of sex and dietary nitrate on COVID-19 vaccine-induced vascular dysfunction in healthy men and women: protocol of the DiNOVasc-COVID-19 study

**DOI:** 10.1186/s13063-023-07616-2

**Published:** 2023-09-16

**Keywords:** COVID-19, Endothelium, Inflammation, Nitrate, Sex, Vascular

## Abstract

**Background:**

Cardiovascular events, driven by endothelial dysfunction, are a recognised complication of COVID-19. SARS-CoV-2 infections remain a persistent concern globally, and an understanding of the mechanisms causing endothelial dysfunction, particularly the role of inflammation, nitric oxide, and whether sex differences exist in this response, is lacking. We have previously demonstrated important sex differences in the inflammatory response and its impact on endothelial function and separately that the ingestion of inorganic nitrate can protect the endothelium against this dysfunction. In this study, we will investigate whether sex or a dietary inorganic nitrate intervention modulates endothelial function and inflammatory responses after the COVID-19 vaccine.

**Methods:**

DiNOVasc-COVID-19 is a double-blind, randomised, single-centre, placebo-controlled clinical trial. A total of 98 healthy volunteers (49 males and 49 females) will be recruited. Participants will be randomised into 1 of 2 sub-studies: *part A* or *part B*. *Part A* will investigate the effects of sex on vascular and inflammatory responses to the COVID-19 vaccine. *Part B* will investigate the effects of sex and dietary inorganic nitrate on vascular and inflammatory responses to the COVID-19 vaccine. In *part B*, participants will be randomised to receive 3 days of either nitrate-containing beetroot juice (intervention) or nitrate-deplete beetroot juice (placebo). The primary outcome for both sub-studies is a comparison of the change in flow-mediated dilatation (FMD) from baseline after COVID-19 vaccination. The study has a power of > 80% to assess the primary endpoint. Secondary endpoints include change from baseline in inflammatory and leukocyte counts and in pulse wave analysis (PWA) and pulse wave velocity (PWV) following the COVID-19 vaccination.

**Discussion:**

This study aims to evaluate whether sex or dietary influences endothelial function and inflammatory responses in healthy volunteers after receiving the COVID-19 vaccine.

**Trial registration:**

ClinicalTrials.gov NCT04889274. Registered on 5 May 2023. The study was approved by the South Central – Oxford C Research Ethics Committee (21/SC/0154).

**Supplementary Information:**

The online version contains supplementary material available at 10.1186/s13063-023-07616-2.

## Background

Patients with pre-existing cardiovascular disease (CVD) are at greater risk of severe COVID-19 and worse outcomes [1–4]. Additionally, there has been increasing recognition of specific cardiovascular complications of COVID-19 including acute coronary syndromes and myocarditis, amongst others [5–9]. Importantly, the incidence of such cardiovascular complications is greater in men than in women [10, 11]. The mechanisms underlying these cardiovascular manifestations might be secondary to the severe inflammatory response induced by COVID-19, as well as the virus itself. These might result in endothelial dysfunction [12, 13], thus inducing hyperinflammatory and hypercoagulable states [14]. In health, the endothelium exhibits anti-inflammatory and antithrombotic properties that prevent vascular inflammation and opposes thrombogenesis [15], effects mediated predominantly by the soluble mediator nitric oxide (NO) [16–18]. In disease, the systemic inflammatory response and subsequent endothelial dysfunction reduce NO bioavailability [19]. Recently, we have demonstrated that inorganic nitrate can mitigate against typhoid vaccine-induced endothelial dysfunction, with suppression of pro-inflammatory cell types, and simultaneously enhance the resolution of inflammation with increased expression of anti-inflammatory cytokines and chemokines [20]. It is possible that the prevalence of endothelial dysfunction also contributes to the severity of COVID-19 disease.

Thus, to study the impact of systemic inflammation (related to COVID-19) upon endothelial function, in men and women, we have assessed vascular reactivity in both sexes prior to and following COVID-19 vaccination, and assessed whether augmentation of NO levels, via delivery of dietary inorganic nitrate which augments NO via activation of the non-canonical pathway [21], improves endothelial function where dysfunction is evident.

## Methods and design

### Trial objectives

Aims of research: We wish to test whether sex differences exist in inflammatory responses and thereby vascular function after delivery of the COVID-19 vaccine, as a model of endothelial dysfunction induced by COVID-19. Secondly, we also wish to determine whether inorganic nitrate supplementation protects against endothelial dysfunction in this COVID-19 setting.

### Participant selection

This is a single-centre study and participants will be recruited from the Barts Health NHS Trust catchment area, including all NHS-approved vaccination hubs. In addition, we will identify participants from Queen Mary University of London and Barts and The London Faculty of Medicine and Dentistry.

### Original hypothesis

We hypothesise that the COVID-19 vaccine will induce inflammatory responses and thus endothelial dysfunction. However, we expect women to be protected against vascular dysfunction and hypothesise that dietary inorganic nitrate will attenuate the consequent vascular dysfunction following the delivery of the COVID-19 vaccine.

### Primary endpoints

Part AComparison between the sexes of the change in flow-mediated dilatation (FMD) from the baseline FMD response after COVID-19 vaccination 

Part BComparison of change in FMD from baseline after COVID-19 vaccination following inorganic nitrate versus placebo supplementationComparison of change in plasma nitrite concentration ([NO_2_^−^]) following inorganic nitrate versus placebo supplementation

### Secondary endpoints

Comparison of change in peripheral markers of inflammation and leucocyte count following COVID-19 vaccination between the sexesComparison of change in peripheral markers of inflammation and leucocyte count following COVID-19 vaccination and nitrate versus placebo supplementationComparison of change in PWV from baseline following COVID-19 vaccination and nitrate versus placebo supplementationComparison of change in PWA from baseline following COVID-19 vaccination and nitrate versus placebo supplementationComparison of GTN-induced vasodilation in the brachial artery from baseline following COVID-19 vaccination and nitrate versus placebo supplementation

### Inclusion criteria

Healthy volunteers with either a confirmed booking or a plan to book their 1st COVID-19 vaccination or due delivery of a 2nd or booster dose of any COVID-19 vaccine within the upcoming 92 days, as per government guidelinesAged 18–60Volunteers willing to sign the consent form

### Exclusion criteria

Healthy subjects unwilling to consentPregnant or any possibility that a subject may be pregnantHistory of any serious illnesses (such as diabetes, cardiovascular disease, respiratory diseases including asthma and chronic obstructive airways disease, autoimmune conditions, and any condition which requires treatment with medication), including recent infections or traumaSubjects taking systemic medication (other than the oral contraceptive pill)Subjects with self-reported use of mouthwash or tongue scrapesSubjects with recent (2 weeks) or current antibiotic useSubjects with a history or recent treatment of (within the last 3 months) any oral condition (excluding caries), including gingivitis, periodontitis, and halitosisSubjects with a history of COVID-19 vaccination within the preceding 28 daysSubjects with any history of a blood-borne infectious disease such as hepatitis B or C virus or HIV

### Study design and intervention

This is a prospective double-blind, placebo-controlled, clinical study. A total of 98 healthy volunteers (male and female, aged 18–60) as per inclusion criteria will be recruited following the provision of consent (model consent form added as Supplementary Document). Figure 1 shows a summary of the study scheme. Figure 2 shows the SPIRIT figure summary of the study. Participants will be screened having either booked their COVID-19 vaccination or have a plan to do so in the upcoming 92 days. Participants are able to receive any vaccine manufacturer or a combination available to them (with the manufacturer recorded in the case report form). Screening will take place virtually or in person. Participants will be randomised into 1 of 2 parts of the study. Both study parts will take place at the William Harvey Clinical Research Centre, Queen Mary University of London, Barts and The London Faculty of Medicine and Dentistry. Participants will be eligible for inclusion if they do not suffer from any illnesses that require the use of prescription medication (other than the oral contraceptive pill), and thus, the use of prescription medicines will exclude them from the study. Furthermore, following randomisation, the participant will still be eligible to undergo usual care should they require it during the study including concomitant planned and unplanned medical care (unrelated to the study itself) and medication for the time period of the physical visits and biological sampling; such an event would exclude them from the study. All events will be recorded in the case report form.

**Fig. 1 Fig1:**
[figure not shown]
DiNOVasc-COVID-19 study summary scheme. BP, blood pressure; COVID-19, coronavirus disease 2019; NHS, National Health Service; PWA, pulse wave analysis; PWV, pulse wave velocity

**Fig. 2 Fig2:**
[figure not shown]
SPIRIT figure. Summary SPIRIT figure showing the visit structure and events during the clinical study

*Part A:* 15 men and 15 women will be randomised into *part A*. This part of the study will recruit equal numbers of men and women to compare the influence of biological sex on inflammatory responses and vascular function following the COVID-19 vaccine.

*Part B*: 34 men and 34 women will be randomised into *part B*. In this study, we will recruit equal numbers of men and women and make comparisons of the effects of dietary inorganic nitrate and sex on vascular function and inflammatory responses. After randomisation into *part B*, participants will undergo further randomisation to receive either 70 mL of a nitrate-containing beetroot juice (5–6 mmol, James White Drinks Ltd., UK, Beet It^®^ Sport Nitrate 400 Shot) or nitrate-deplete placebo control.

Baseline measurements of BP, PWA, PWV, FMD, blood, urine, and saliva will be taken at *visit 2*. Participants randomised to *part B* will begin taking a daily dose of the beetroot juice 2 days before receiving their COVID-19 vaccination and consume 3 consecutive daily doses. The last dose will be taken on the morning of the vaccine. All participants will receive their COVID-19 vaccination on the morning of *visit 3* and return to the clinical research facility to undergo repeat measurements of BP, PWA, PWV, FMD, blood, urine, and saliva 8 ± 2 h after the vaccine. *Visit 4* will occur 28 ± 1 days after delivery of the vaccine, at which point participants will be asked to complete a bespoke experience questionnaire. This questionnaire is bespoke and has been tailored to capture specific aspects of symptoms before and after the COVID-19 vaccination and scored from 0 to 10. These include general health, anxiety and stress, fatigue, and muscle/joint pain. We have also incorporated a rating on the experience of the intervention/placebo and included yes/no questions for whether the juice intervention/placebo was easily incorporated into their daily routine and whether the participant would be keen to continue the intervention as a lifestyle measure if found to be beneficial.

Patients will be recruited throughout all waves of the COVID-19 pandemic. Timing of when COVID-19 vaccination and previous COVID-19 infection will be obtained, to permit exploratory analyses of differences between COVID-19 waves and/or the presence of previous COVID-19 infections.

### Randomisation and blinding process

A total of 98 healthy volunteers will be recruited. *Part A* is an observational study in which 15 males and 15 females will be recruited. *Part B* is a double-blind, randomised, placebo-controlled clinical trial and will enrol 34 males and 34 females. Randomisation into *parts A* and *B* will occur in a 1:2 fashion using block randomisation, such that recruitment occurs over a similar timespan.

In *part B*, 1:1 block randomisation will be used to allocate participants to nitrate-containing beetroot juice or nitrate-deplete beetroot juice (placebo). The treatment assignment of the volunteers will remain blinded until the end of the study, at which point the study will be unblinded. If emergency unblinding is required, the chief investigator will be informed. A list of the unblinded treatment allocations will be stored in a secure location at the William Harvey Clinical Research Centre and be available at all times.

### Study start and end dates

Recruitment commenced on 21 April 2021. The provisional end date of the study is April 2024.

### Methods to be used

All sample analyses will be conducted blind to group allocation.

#### Blood, urine, and saliva analysis

Venous blood samples will be acquired, and plasma will be stored at − 80 °C for exploratory analyses. Blood samples will be sent for clinical haematological and biochemical analysis. From a separate blood sample, polymorphonuclear leucocytes (PMNs) and peripheral blood mononuclear cells (PBMCs) will be isolated.

Flow cytometry will be used to assess platelet activation and platelet leukocyte aggregates (CD42b, CD14, CD16b, CD16). Platelet P-selectin (CD62P) expression and platelet number will be determined using cell counting beads (Thermo Fisher). Platelet P-selectin expression in response to agonists, collagen (with HEPES buffer solution), and ADP will be assessed. Platelet aggregation responses to the platelet stimuli (ADP and collagen) will be assessed using a Multiplate^®^ aggregometer reader.

Total RNA will be extracted from isolated PMNs and PBMCs using a RNeasy^®^ Mini Kit according to the manufacturer’s instructions (including DNAse treatment) (Qiagen, Hilden, Germany).

Saliva samples will be centrifuged, and a pellet generated, which will contain the genetic material of the oral microbiota. A saliva sample will also be collected for human genomic sequencing using an Oragene^®^ OG-600 human saliva DNA storage kit (DNA Genotek™, Canada).

Plasma, urine, and saliva nitrate/nitrite concentration will be determined using liquid-phase ozone chemiluminescence as previously described [22, 23]. A sample of juice from each participant in *part B* will be acquired, and nitrate and nitrite quantified using the same methods. All measurements will be conducted by an individual blinded to the intervention allocations.

#### Pulse wave analysis and pulse wave velocity

PWA and PWV are non-invasive measures of arterial stiffness and compliance. PWA and PWV are quantified using a Vicorder^®^ device (Skidmore Medical Ltd., UK). PWA will be assessed by applying a cuff to the non-dominant arm, with the participant lying in the supine position. PWV will be determined by placing a cuff around both the femoral and carotid arteries simultaneously. The cuffs are inflated to ~ 65 mmHg, and the corresponding oscillometric signal from each cuff is digitally analysed to extract the pulse time delay. The aortic length is estimated by measuring the distance between the femoral cuff and the supra-sternal notch. PWV is calculated by using the formula: PWV = aortic distance/pulse time delay [24].

#### Flow-mediated dilatation

FMD is a non-invasive method of measuring endothelial function in vivo [25]. The technique uses vascular ultrasound to measure the luminal dimension of the brachial artery, which dilates following a period of limb ischaemia, owing to the release of several endothelial factors, including NO [26]. This will be performed in accordance with recently published guidelines [27]. A high-resolution external vascular ultrasound Siemens/Acuson Sequoia C256 Colour Doppler, with a 7.0-MHz linear-array transducer supported by a stereotactic clamp, will be used to image the brachial artery with the patient lying in a supine position. The brachial artery will be visualised in longitudinal section. The image is projected onto automated edge detection software (FMD Studio, Cardiovascular Suite, Quipo Srl., Italy). The edge detection algorithm tracks the vascular intima in real time providing an automated and unbiased assessment of brachial artery diameter with automated FMD calculation. A pulse-wave Doppler sample volume is placed centrally within the lumen of the vessel and calibrated to record real-time shear rate. A pneumatic cuff is placed over the upper forearm and inflated to 300 mmHg for 5 min. The cuff is then released, and the brachial artery is observed for a further 5 min. FMD is defined as the percentage increase in vessel diameter after the release of the pneumatic cuff.

Following the measurement of FMD, 0.4 mg of sublingual glyceryl trinitrate (GTN) will be administered, and the luminal diameter of the brachial artery will be measured for a period of 5 min to assess GTN-induced smooth muscle-mediated brachial artery dilatation.

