### Sample size determination and statistical analysis

In this study, we aim to recruit 98 participants, with 30 healthy volunteers in *part A* and 64 in *part B*. This sample size will empower the study to test the primary endpoint.

These numbers have been based upon our previous experience with typhoid vaccination which causes a reduction in FMD of ~ 1.5% absolute units which is a reduction of approximately 25% of the response [28]. We have previously identified sex differences in the response to typhoid vaccine, with a change from baseline of FMD of − 0.5 (SD = 2.4) in men and 2.4 (SD = 2.5) in women [29]. For *part A*, using these data, if we use a conservative effect size of 25% less than that achieved in our previously published study, 13 participants are required in each group to provide 90% power for the primary outcome. To account for potential dropouts of ~ 10%, 15 participants will be recruited into each group and thus 30 volunteers in total. For the analysis of *part A*, a linear regression model will be used to compare changes in vascular dysfunction pre- to post-vaccination between the sexes, unadjusted and adjusted for important risk factors including age, body mass index, and baseline vessel diameter.

Our unpublished preliminary data investigating the effects of dietary inorganic nitrate on vascular responses (FMD) has identified a decrease in FMD from baseline of 1.4 (SD = 1.5) with typhoid vaccine and with dietary nitrate intervention only 0.08 (SD = 1.7) [20]. Based on these data, for the primary outcome of change in FMD, 25 participants will be required in each group at an 80% power, to observe a difference between the intervention arms. To observe the differences between the sexes, 30 in each group provides a 90% power, which will also offer a > 95% power to detect a rise in [NO_2_^−^], as observed in previous studies [30]. To account for potential dropouts of ~ 10%, a total of 68 volunteers will be recruited. For the statistical analysis in *part B*, analysis of covariance (ANCOVA) will be used to compare the change in vascular dysfunction pre- to post-vaccination, between dietary nitrate and placebo control groups adjusting for pre-vaccination level, and to compare the change in plasma [NO_2_^−^] between the dietary nitrate and placebo control groups.

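### Part B's FMD ANCOVA omits age, BMI and baseline vessel diameter, which Part A treats as important, and gives up some precision; the post-dose diameter denominator warrants a supportive check only

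*Protocol article*

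**What the plan says.** The Flow-mediated dilatation section defines the outcome as a percentage: "FMD is defined as the percentage increase in vessel diameter after the release of the pneumatic cuff". It also describes a Doppler sample volume "calibrated to record real-time shear rate", so diameter and shear are both recorded.

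Under Study design and intervention, baseline measurements are taken at visit 2. Part B participants then take juice daily for three days, the last dose on the vaccine morning. FMD is repeated at visit 3, 8 ± 2 h after the vaccine.

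The section on sample size and statistical analysis fixes both models. Part A uses linear regression, unadjusted and also "adjusted for important risk factors including age, body mass index, and baseline vessel diameter". Part B uses ANCOVA on the change in FMD "between dietary nitrate and placebo control groups adjusting for pre-vaccination level", with no further covariate named.

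The Part B sample size assumes "a decrease in FMD from baseline of 1.4" ("SD = 1.5) with typhoid vaccine") and, "with dietary nitrate intervention only 0.08" (SD 1.7). It concludes that "25 participants will be required in each group at an 80% power, to observe a difference between the intervention arms".

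**The concern.** Two separate matters arise.

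**Precision.** The article calls age, BMI and baseline vessel diameter important for change in FMD in one part of the study and leaves them out of the model for the same outcome in the other. All three are pre-treatment values, so including them in a randomised comparison introduces no bias from treatment. If they predict the outcome, leaving them out widens the confidence interval for no gain.

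**Interpretation.** Percentage FMD is naturally read as relative to the resting diameter of the same visit. In Part B the visit 3 resting diameter is measured after a supplement that the Background says augments NO, and NO is among the factors the article names as dilating this artery. If the resting artery were larger in the nitrate arm, percentage FMD could fall for arithmetical reasons. No Part B endpoint or analysis stated in the article uses resting diameter or shear, so the result would be harder to interpret if that happened.

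**Working it through.** **1. Reproduce the plan's own figure.** Inputs are from the sample size section; alpha is not given there, so two-sided 0.05 is assumed.
- Planned difference = 1.4 - 0.08 = 1.32 points.
- Pooled SD = sqrt((1.5² + 1.7²)/2) = 1.603; standardised effect = 1.32/1.603 = 0.823.
- A two-sample t-test at 80% power needs 24.15, so 25 per arm. This agrees with the stated 25.
- At 30 per arm, power is 88.0% (t) or 89.0% (normal approximation), close to the stated 90%. The article words that 90% as being for the comparison of the sexes.
- 30/0.9 = 33.3, so 34 per arm and 68 in total, as planned.

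**2. Precision from the omitted covariates.** If they explain a share R² of the residual variance, the SD becomes 1.603 × sqrt(1 - R²). The documents give no R², so 5% to 20% is an assumption.

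| R² (assumed) | SD | Power, 25 per arm | Power, 30 per arm |
|---|---|---|---|
| 0 | 1.603 | 81.4% | 88.0% |
| 5% | 1.563 | 83.3% | 89.6% |
| 10% | 1.521 | 85.2% | 91.1% |
| 20% | 1.434 | 89.0% | 93.9% |

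Losing a few degrees of freedom lowers these figures by about 0.1 percentage points. The SD of 1.603 is that of the raw change. Any gain from adjusting for baseline FMD comes on top, and R² here means variance explained beyond baseline FMD.

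**3. Sensitivity of percentage FMD to resting diameter.** FMD = peak/rest - 1. The article equates a fall of about 1.5 points with about 25% of the response, which implies a baseline near 1.5/0.25 = 6%. Starting from the nitrate arm's planned value, 6 - 0.08 = 5.92%, let resting diameter rise by x and let a fraction c of that rise, in absolute terms, carry through to the peak:

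FMD = (1.0592 + c·x)/(1 + x) - 1.

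For x = 1.25%:

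| What the peak does | Change in FMD (points) | x that would offset 1.32 points |
|---|---|---|
| Scales in proportion to rest | 0 | none |
| Absolute dilatation preserved (c = 1) | -0.07 | 28.7% |
| c = 0.75 | -0.38 | 4.5% |
| c = 0.5 | -0.69 | 2.4% |
| c = 0.25 | -1.00 | 1.7% |
| Peak fixed (c = 0) | -1.31 | 1.26% |

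The fixed-peak offset is insensitive to baseline FMD: 1.29% at a baseline of 4% and 1.22% at 10%. The assumption about the peak drives the result, and the documents say nothing on it.

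**4. What each covariate can do.** Visit 2 diameter is measured before any juice. It can reduce residual variance but cannot remove a shift that arises after dosing. Visit 3 diameter could expose such a shift, but it is post-randomisation, and conditioning on it changes what is being estimated.

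**The case against.** The strongest reply is that nothing here is wrong. Part A is observational and compares the sexes, so it needs confounder adjustment. Part B is randomised, and ANCOVA on baseline FMD alone gives a valid contrast, so different covariate sets are not a contradiction. That stands, and the point is about efficiency. Nor is the trial short of power: at 30 per arm it has about 88% without the extra covariates.

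It can also be said that supportive models and by-arm diameter summaries are ordinary analysis-plan detail, and that no analysis plan is shown. That is fair for the supportive analyses, which may already be planned. It is weaker for the ANCOVA, because the article itself states that model's adjustment.

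A reader might go further and infer that a resting dilatation of about 1.25% could cancel the whole planned benefit, so that a null result could not be told from a masked protective effect. The documents do not support this, for four reasons:
- The figure needs the peak diameter to stay exactly fixed, which nothing in the article states. If absolute dilatation is preserved, the same rise costs 0.07 points, about 5% of 1.32.
- No section says that nitrate enlarges the resting brachial artery. The GTN procedure shows that an NO donor can dilate it within minutes, which says little about FMD measured 8 ± 2 h after the vaccine.
- The 1.32 points come from earlier FMD data under nitrate. If those used the same percentage metric, as seems natural though unstated, any diameter effect is already inside the 1.32, and setting it against that figure again would count it twice.
- GTN-induced dilatation, nitrate versus placebo, is a secondary endpoint and gives partial information on smooth-muscle response.

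**Conclusion.** The firm finding is a modest, avoidable loss of precision. Part B's stated ANCOVA leaves out three baseline variables that the same section treats as important for the same outcome. Under the assumed R² of 5% to 20%, including them would raise power from about 88% to about 90%-94% at 30 per arm, or from 81% to 83%-89% at 25 per arm. This rests on two-sided 0.05, the article's planning SDs and an R² for which the documents give no source. Validity is not in question.

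The denominator issue is an open question of interpretation, not a demonstrated bias. For a 1.25% rise in resting diameter the shift runs from 0 through -0.07 to about -1.3 points, and the documents do not say where in that range the truth lies or whether any rise occurs. It justifies an inexpensive supportive check and no change to the primary endpoint.

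**What to change.** 1. Keep change in percentage FMD as the Part B FMD primary endpoint.
2. Add visit 2 resting diameter, age and BMI to the Part B ANCOVA alongside pre-vaccination FMD, and state that the purpose is precision.
3. As supportive analyses, report resting diameter and absolute dilatation in mm by arm and visit, and change in shear by arm. Prespecify a log-diameter (allometric) sensitivity analysis, with log peak diameter as outcome and log resting diameter of the same visit as covariate. Label it supportive because visit 3 diameter is post-randomisation.
4. If a sensitivity figure for resting diameter is quoted, give the whole range and the assumption about peak diameter behind each value.

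The cost is three degrees of freedom in the primary model, some analysis-plan wording and a few extra models. Diameter and shear are already recorded. Age and BMI are needed for Part A, and I assume they are collected in the same way in Part B. No new visits or participants are needed. Trial status reports that all 98 participants have had their baseline visit, and Dissemination says primary analysis begins straight after the last visit, so the change should be documented before unblinding.
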